#### 3.1.1 Selection of Principal Investigator and other investigators at sites

Sites must have an appropriate Principal Investigator (PI) i.e. a health care professional authorised by the site and ethics committee to lead and coordinate the work of the trial on behalf of the site. Other investigators at site wishing to participate in the trial must be trained and approved by the PI. All investigators must have experience of treating glioblastoma, have consultant status and routinely present cases to a Multi-Disciplinary Team.

Once the site has been activated by UCL CTC, the PI is responsible for ensuring:

- Adherence to the most recent version of the protocol
- All relevant site staff are trained in the protocol requirements
- Appropriate recruitment and medical care of patients in the trial
- Timely completion and return of CRFs
- Prompt notification and assessment of all adverse events
- Storage and shipment of biological samples where applicable

### 3.2 Site initiation and activation

#### 3.2.1 Site initiation

Site initiation will be performed for each site by a site visit.

The following documentation must be in place prior to a site being opened to recruitment by UCL CTC trial team:

- Trial specific Declaration of Participation/Site Registration Form including signature and delegation log (completed by all members of the core trial team at the site (research nurses, trial administrators, lead pharmacy staff responsible for the trial), and signed off by the Principal investigator)
- All relevant institutional approvals (e.g. local NHS permission)
- A signed Clinical Trial Site Agreement (CTSA) between the Sponsor and the relevant institution (usually a NHS Trust)

The PI, other delegated site investigators and all staff involved in the conduct of the trial at the site must be identified on the site delegation log held at site and copied to UCL CTC prior to site activation.

Sites must also have in place facilities for providing **24 hour medical advice** for trial patients.

### 3.2.2 Site activation

Once the trial team at UCL CTC have confirmed that all documentation is in place a site activation letter will be issued to the Principal Investigator, at which point the site may start to approach patients.

---

## 4.0 Informed consent

Sites are responsible for assessing a patient's capability to give informed consent.

Sites are responsible for ensuring all patients have been given the current version of the patient information sheet, are fully informed about the trial and have confirmed their willingness to take part in the trial by signing a consent form. In addition to the consent form to indicate consent to the trial, there are additional consent forms to indicate that the patient is willing to donate any of the optional biological specimens for the trial (archival biopsy samples, blood samples throughout the trial, and/or a post mortem tumour sample). The PI or other delegated site staff are required to provide a full explanation of the trial and all relevant treatment options to each patient prior to trial entry. During these discussions the current detailed patient information sheet for the trial will be given to the patient. A minimum of twenty four hours must be allowed for the patient to consider and discuss participation in the trial. Written informed consent on the current version of the consent forms for the trial must be obtained before any trial-specific procedures are conducted.

For patients in this trial, consent will also be obtained from the patient's named carer, because the carer may be required to assist with CRF completion should the patient's condition deteriorate or in the event that the patient is unable to speak or write. In these circumstances the carer may give answers on behalf of the patient for questions regarding quality of life, Karnofsky performance score, health economics, and adverse events.

Site staff are responsible for:

- checking that information on the consent forms are complete and legible
- checking that the patient has completed/initialled all relevant sections and signed and dated the form
- Checking that an appropriate member of staff has countersigned and dated the consent forms to confirm that they provided information to the patient
- Checking that an appropriate member of staff has made dated entries in the patient's medical notes relating to the informed consent process (i.e. info given, consent signed etc.)
- Adding the patient trial number to all copies of the consent form

The original signed consent form and a copy must be stored at site (in the Investigator Site File and the patient's medical notes). A further copy must be given to the patient.

The right of the patient to refuse to participate in the trial without giving reasons must be respected. All patients are free to withdraw at any time (see [section 13.0](#) – withdrawal of patients).

## 5.0 Selection of Patients

### 5.1 Patient Eligibility

There will be no exception to the eligibility requirements at the time of randomisation. Queries in relation to the eligibility criteria should be addressed prior to calling/faxing for randomisation. Patients are eligible for the trial if all the inclusion criteria are met and none of the exclusion criteria applies.

#### 5.1.1 Inclusion Criteria

For inclusion in the clinical trial, patients must fulfil all of the following criteria:

- Provision of informed consent
- Age  $\geq 18$  years
- Life expectancy  $\geq 12$  weeks
- Histological/cytological confirmation of glioblastoma (WHO grade IV)
- Patients with measurable disease (contrast-enhancing tumour  $\geq 10$  mm by shortest diameter on 2 axial slices) by MRI imaging within 7 days prior to enrolment. (If patients have recently had a routine MRI scan, this should be assessed before deciding whether or not to screen the patient, and booking the screening/baseline MRI.)
- Patients must have been on no steroids or a stable dose of steroids (dexamethasone) for at least 5 days before the baseline MRI
- Patients must have completed standard first-line treatment for glioblastoma including surgery (with exception, if patient does not receive surgery as part of first-line treatment due to anatomical location, based on neurosurgeon's assessment), cranial radiotherapy and chemotherapy with concomitant temozolomide.
  - It is not essential that the entire Stupp regimen of 6 cycles of adjuvant temozolomide following chemoradiotherapy has been completed.
  - The last dose of temozolomide must be more than 28 days from enrolment.
  - Gliadel® wafers are permitted, as it is part of local treatment.
  - No other previous treatment for glioblastoma is permitted (other than steroids).

- Patients must have a Karnofsky Performance Score of 70 or above
- Patients must have a mini-mental status examination score of 15 or greater
- Patients who require either oral anticoagulants (coumadin, warfarin) or low molecular weight heparin are eligible provided there is increased vigilance with respect to monitoring INR.

For inclusion in the genetic research, patients must fulfil the following criterion:

- Provision of informed consent for genetic research (separate consent required for tumour biopsy, blood sample, and post mortem donations)

If a patient declines to participate in any of the genetic research, there will be no penalty or loss of benefit to the patient. The patient will not be excluded from other aspects of the study described in this Clinical Study Protocol, so long as they consent to the main study.

### 5.1.2 Exclusion Criteria

Any of the following is regarded as a criterion for exclusion from the study:

- Patients on enzyme-inducing anti-epileptic drugs (see [section 7.5](#)) within 2 weeks prior to study enrolment. Note: Patients are eligible if they switched to non-enzyme inducing agents and discontinued enzyme-inducing agents for more than or equal to 2 weeks prior to randomisation
- Inadequate bone marrow reserve as demonstrated by an absolute neutrophil count  $\leq 1.5 \times 10^9$  /L or platelet count  $\leq 100 \times 10^9$  /L or requiring regular blood transfusions to maintain haemoglobin  $>9\text{g/dL}$
- Serum bilirubin  $\geq 1.5 \times \text{ULRR}$  (except for patients with known documented cases of Gilbert's Syndrome)
- ALT or AST  $\geq 5 \times \text{ULRR}$
- Serum creatinine  $>1.5 \times \text{ULRR}$  or a creatinine clearance of  $\leq 50\text{mL/min}$  calculated by Cockcroft-Gault

- Greater than +1 proteinuria on two consecutive dipsticks taken no less than 1 week apart unless urinary protein <1.5g in a 24 hr period or UPC (Urine Protein: Creatinine) ratio <1.5
- History of significant gastrointestinal impairment, as judged by the investigator, that would significantly affect the absorption of cediranib or gefitinib, including the ability to swallow the tablet whole
- Patients with a history of poorly controlled hypertension with resting blood pressure >150/100mmHg in the presence or absence of a stable regimen of anti-hypertensive therapy, or patients who are requiring maximal doses of calcium channel blockers to stabilise blood pressure
- Any evidence of severe or uncontrolled diseases (e.g. unstable or uncompensated respiratory, cardiac, hepatic or renal disease)
- Unresolved toxicity >CTC AE grade 1 from previous anti-cancer therapy (including radiotherapy) except alopecia (if applicable)
- Mean QTc with Bazetts correction >470msec in screening ECG or history of familial, long QT syndrome (see Appendix 7)
- Cardiac ventricular arrhythmias requiring anti-arrhythmic therapy
- Significant haemorrhage (>30mL bleeding/episode in previous 3 months) or haemoptysis (>5mL fresh blood in previous 4 weeks)
- Recent (<14 days) major surgery or brain biopsy. Recent craniotomy (<28 days) prior to first dose, or a surgical incision that is not fully healed
- Pregnant or breast-feeding women or women of childbearing potential with a positive pregnancy test prior to receiving study medication (see [section 5.1.3](#))
- Known hypersensitivity to cediranib, gefitinib or any of its excipients
- History of other malignancies (except for adequately treated basal or squamous cell carcinoma or carcinoma *in situ*) within 5 years, unless the patient has been disease free for 2 years and they have tissue diagnosis of the target lesion
- Known infection with hepatitis B or C or HIV

- 
- Involvement in the planning and conduct of the study (applies to both UCL CTC, AstraZeneca staff and staff at the study site)
  - Past medical history of interstitial lung disease, idiopathic pulmonary fibrosis, drug-induced interstitial disease, radiation pneumonitis which required steroid treatment or any evidence of clinically active interstitial lung disease
  - Previous enrolment as part of the present study
  - Treatment with an investigational drug within 30 days prior to the first dose of cediranib/gefitinib
  - Other concomitant anti-cancer therapy except steroids (dexamethasone only)
  - Previous anti-angiogenesis (e.g. bevacizumab, sorafenib, sunitinib) therapy
  - Previous anti-EGFR treatments (e.g. cetuximab, panitumumab or small molecule tyrosine kinase inhibitors etc.) or downstream targets e.g. mTOR inhibitors.
  - Patients with evidence of any intratumoural or peritumoural haemorrhage deemed significant by the treating physician
  - Patients who have received any form of cranial radiation within 3 months prior to study entry (excluding imaging)
  - Patients who have progressed within 3 months of completion of standard cranial radiation
  - Patients that have received radiosurgery or brachytherapy
  - Patients on >8mg/day dexamethasone or equivalent steroids on any day of the 2 weeks prior to randomisation

## Restrictions

- For elective surgery during the study, or any procedure that carries a risk of internal bleeding, it is recommended that cediranib be stopped for 2 consecutive weeks prior to the surgical procedure. Cediranib treatment can be restarted when the surgical wound has healed. If emergency surgery is performed, precautions should be taken to minimise the potential risk of bleeding and thrombosis associated with this class of agents, cediranib should be stopped and

close monitoring for bleeding, wound healing and thromboembolic complications should be initiated. Patients should not receive cediranib within 2 weeks of major surgery.

- Caution in the concomitant use of any medication that may markedly affect renal function. Such medications may be used with caution if deemed essential for treatment or may be continued if already in use prior to entry in the study with no effect on renal function.
- Caution should be exercised in concomitant use of any medication that may significantly affect hepatic P450 drug metabolising activity by way of enzyme induction or inhibition within 2 weeks of the first dose of cediranib or gefitinib and throughout the study period (see Appendix 3 for a list of drugs)
- Patients who are blood donors should not donate blood during the study and for 3 months following their last dose of study treatment
- Medicinal products that cause significant sustained elevation in gastric pH, such as proton pump inhibitors and h2 antagonists may reduce bioavailability and plasma concentrations of gefitinib and therefore, may reduce efficacy. Antacids if taken regularly close in time to administration of gefitinib may have a similar effect. These should be avoided where possible.
- Patients should take their medication at least 1 hour prior to the consumption of a meal or at least 2 hours after a meal has been ingested.

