## 7.0 Trial Treatment

### 7.1 Treatment summary

For the purpose of this protocol, the active IMPs are cediranib and gefitinib, with gefitinib-matched placebo.

Enrolled subjects will be randomised to receive **either** cediranib 30mg od orally and gefitinib 500mg od orally **or** cediranib 30mg od plus placebo. Each cycle of treatment lasts 6 weeks.

Treatment will continue until confirmation of progression as defined in 2.6.1.1, patient decision or the development of unacceptable toxicity (if there is radiological progression only treatment can continue if the investigator has the opinion that the patient is receiving benefit. It is not compulsory to stop trial treatment at any indication of radiological progression, even at confirmed radiological progression on multiple scans if it is felt that the patient is receiving benefit. Investigators should be wary of pseudoprogression on MRI scans.).

If none of the above are thought to have occurred on the last day of the treatment cycle, the patient will start the next cycle of treatment the following day. Treatment pauses of up to 14 days are permitted (21 days are permitted in consultation with the CI) but should be recorded on the next CRF. Treatment delays of longer than 14 days (or 21 days in consultation with the CI) will result in patient withdrawal from the study.

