A maximum of a 14-day (21-day in consultation with the CI) delay in dosing for cediranib is permitted. If a longer interruption is required due to unresolved toxicity, cediranib should be discontinued. In addition, there are certain circumstances in which study medication should be permanently discontinued (see [section 13.1](#)).

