#### 13.1.1 Discontinuation of Trial Drugs

In addition, both trial drugs should be permanently discontinued in patients with the following conditions:

- Gastrointestinal perforation or wound dehiscence requiring medical intervention
- Serious haemorrhage, i.e., requiring medical intervention
- Severe hypertension (see [section 7.4.1.4](#) for hypertension management protocol)
- Nephrotic syndrome
- Severe arterial thromboembolic event
- If any case of RPLS occurs that is confirmed by imaging (CT or MRI), trial drugs should be immediately discontinued, in addition to any other measures to alleviate symptoms and control blood pressure
- Patients should not receive trial drugs within 2 weeks of major surgery. Where possible, trial drugs should be suspended for 2 weeks to allow clearance before major surgery.
- Interstitial lung disease (ILD)
- Severe change in liver function

In these cases patients should continue to have trial assessments for the purposes of follow-up. If a patient wishes to withdraw from trial treatment, sites should explain the importance of remaining on trial follow-up, or failing this of allowing routine follow-up data to be used for trial purposes and for allowing existing collected data to be used.

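### The rules for interrupting treatment around surgery contradict each other: the break described for elective surgery runs past the standard pause limit in section 7.1, and the sections disagree on its consequence and on which drugs stop

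*Protocol*

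**What the plan says.** Surgery is covered in two places. The Restrictions after section 5.1.2 say of elective surgery, or a procedure with a risk of internal bleeding, that "it is recommended that cediranib be stopped for 2 consecutive weeks prior to the surgical procedure". They continue: "Cediranib treatment can be restarted when the surgical wound has healed". After a sentence on emergency surgery, they add: "Patients should not receive cediranib within 2 weeks of major surgery". Only cediranib is named.

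Section 13.1.1 covers both drugs: "Patients should not receive trial drugs within 2 weeks of major surgery", followed by "Where possible, trial drugs should be suspended for 2 weeks to allow clearance before major surgery". These sentences form one item in a list introduced as conditions for which both trial drugs should be permanently discontinued.

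The length of a pause is limited in four places:

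- **Section 7.1** sets the general rule: "Treatment pauses of up to 14 days are permitted (21 days are permitted in consultation with the CI"; a delay beyond that results in withdrawal from the study. The sentence names no cause of delay and makes no exception for surgery.
- **Section 7.4.1**, on toxicity attributable to cediranib, says "A maximum of a 14-day (21-day in consultation with the CI) delay in dosing for cediranib is permitted". It then requires cediranib to be discontinued if unresolved toxicity calls for a longer interruption.
- **Section 8.2, note k** applies the 14- or 21-day limit to delays due to toxicity. If one drug is over the limit, the patient stops that drug and continues the other. Only if both are over the limit is the patient withdrawn.
- **Section 13.1** lists, among possible reasons for withdrawal from treatment, toxicity of grade 3 or above that causes a delay beyond 14 (or 21) days.

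**The concern.** A site that follows the surgical advice can find that it has passed the pause limit by doing so. Section 7.1 then ends the patient's participation, although the Restrictions say that treatment may resume. The alternative is to shorten the surgical break to fit the limit. The Restrictions connect stopping cediranib with bleeding, thrombosis and wound healing, so the conflict bears on patient safety as well as on bookkeeping.

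The sections also give different answers to two simpler questions: whether gefitinib or placebo stops together with cediranib, and whether surgery means a suspension or the end of treatment. In a double-blind comparison of cediranib with and without gefitinib, exposure and discontinuation after surgery would then depend on which section a site reads. Some discontinuations would be caused neither by toxicity nor by progression.

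**Working it through.** No sample-size figure is involved. The check adds the protocol's own intervals and compares them with its own limits.

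**Inputs**

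- Stop before elective surgery: 14 days (Restrictions, as a recommendation; section 13.1.1, where possible).
- Bar around major surgery: 14 days, direction not stated (Restrictions; section 13.1.1).
- Restart: when the wound has healed, with no number of days (Restrictions). Call the healing time *h* days.
- Limit on a pause: 14 days, or 21 days in consultation with the chief investigator (sections 7.1 and 7.4.1).

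**Reading A: the 2-week bar also covers the time after surgery.** The break for elective major surgery is 14 + 14 = 28 days, or longer if the wound has not healed by then.

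- Over the standard limit: 28 − 14 = 14 days.
- Over the extended limit: 28 − 21 = 7 days.

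**Reading B: the bar covers only the time before surgery, or the surgery is not major.** The break is 14 + *h* days.

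| Healing time *h* | Break (days) | Against 14 | Against 21 |
|---|---|---|---|
| 0 | 14 | within | within |
| 1 | 15 | over | within |
| 7 | 21 | over | within |
| 8 | 22 | over | over |

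The standard limit is used up on the day of the operation. The extended limit leaves 21 − 14 = 7 days for healing.

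**Which reading is more natural.** Section 13.1.1 gives the suspension before surgery in a sentence of its own: "trial drugs should be suspended for 2 weeks to allow clearance before major surgery". The preceding sentence, "Patients should not receive trial drugs within 2 weeks of major surgery", would add little if it too meant only the time before. Section 5.1.2 also excludes patients who had major surgery less than 14 days earlier, so the protocol uses a 2-week interval after surgery elsewhere. This supports Reading A but does not prove it.

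**What a break over the limit leads to**

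| Place | Limited to toxicity? | Consequence |
|---|---|---|
| 7.1 | No | Withdrawal from the study |
| 7.4.1 | The consequence is; the maximum is stated in the toxicity section | Cediranib discontinued |
| 8.2, note k | Yes | The delayed drug stops; withdrawal only if both are delayed |
| 13.1 | Yes | Possible reason to stop all trial treatment |

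The same surgical break of more than 21 days therefore means withdrawal under section 7.1, but need not have any consequence under note k or section 13.1.

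**Which drugs, and for how long.** The Restrictions stop cediranib and allow restart. Section 13.1.1 stops both drugs, describes a suspension, and places it under permanent discontinuation. These cannot all be followed as written.

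**The case against.** The strongest reply is that most of the pause rules concern toxicity, not surgery. Section 7.4.1 is a toxicity section, and note k and section 13.1 name toxicity expressly. Under note k, a patient whose cediranib alone is interrupted continues the other drug and is not withdrawn. Section 13.1.2 likewise keeps a patient who stops one drug on the trial assessments. This is correct, and it narrows the point: the general withdrawal rule rests on section 7.1 alone. It does not remove the point, because section 7.1 is the treatment summary and its wording is unrestricted. Under section 13.1.1 both drugs are stopped, so the one-drug argument does not help there.

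Second, the stop before surgery is a recommendation, or applies where possible, and the 28 days depends on Reading A. Both are true. A site could stay within the limit by not following the recommendation, but the protocol should not make its own advice a route to withdrawal. The conflict with the standard limit needs no more than one day of healing.

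Third, the analysis has some protection. Reasons for stopping are recorded (sections 13.1 and 13.1.2), 6-weekly scans are to continue where possible after treatment stops for reasons other than progression, and the primary analysis is by intention to treat (section 16.2). This stands. No loss of power or bias in progression-free survival is claimed.

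A reader might infer that the restart can never take place, or that the limit is broken in every case of surgery. The protocol does not support that. On Reading B, or for surgery that is not major, a break with up to 7 days of healing fits the 21-day allowance. Emergency surgery allows no 14-day stop beforehand, so a 14-day bar afterwards would just meet the standard limit, provided the wound has healed.

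**Conclusion.** The contradiction is real but narrower than a rule that makes restart impossible. A site that follows the recommended stop before elective surgery passes the standard 14-day pause as soon as healing takes a day or more. For elective major surgery the break is about 28 days if the 2-week bar covers the time after the operation: 14 days over the standard limit and 7 over the extended one. That figure rests on Reading A and on the recommendation being followed. On the narrower reading the 21-day allowance is passed only when healing takes 8 days or more.

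Three defects do not depend on which reading is taken:

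- Section 7.1 is general, while the other limits or their consequences are tied to toxicity.
- The Restrictions and section 13.1.1 name different drugs.
- Section 13.1.1 lists a suspension under permanent discontinuation.

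The protocol gives no rate of surgery during treatment, so the number of patients affected cannot be derived; any percentage applied to the 112 patients would be a guess. The case for correction rests on conflicting instructions that bear on patient safety, not on a statistical effect.

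**What to change.** Reconcile the Restrictions after section 5.1.2 with sections 7.1, 7.4.1, 8.2 (note k), 13.1 and 13.1.1, and check the matching gefitinib limit in section 7.4.2. The reconciled text should:

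1. State whether an interruption for surgery counts towards the 14- or 21-day limit, and whether the withdrawal rule in section 7.1 applies to every cause of delay or to toxicity only.
2. State whether passing the limit on one drug ends that drug or the patient's participation, in the same terms in section 7.1 and note k.
3. Say whether the 2-week bar around major surgery refers to the time before the operation, after it, or both.
4. Name the same drug or drugs in the Restrictions and section 13.1.1.
5. Make both places agree on whether surgery means suspension or permanent discontinuation, and place the item in section 13.1.1 accordingly.

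The sponsor's clinicians decide the durations and the rule; this review proposes neither. The cost is a few sentences in an amendment. Sample size, assessments and the analysis do not change.
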